## Abstract

**Background:**

Durable ventricular assist device (VAD) therapy is reserved for patients with advanced heart failure who have a poor estimated 1-year survival. However, despite highly protocolized management processes, patients are at a unique risk for developing a health care–associated infection (HAI). Few studies have examined optimal strategies for HAI prevention after durable VAD implantation, despite variability in rates across centers and their impact on short- and long-term outcomes.

**Objective:**

The objective of this study is to develop recommendations for preventing the most significant HAIs after durable VAD implantation. The study has 3 specific aims: (1) identify determinants of center-level variability in HAI rates, (2) develop comprehensive understanding of barriers and facilitators for achieving low center-level HAI rates, and (3) develop and disseminate a best practices toolkit for preventing HAIs that accommodates various center contexts.

**Methods:**

This is a sequential mixed methods study starting with a cross-sectional assessment of current practices. To address aim 1, we will conduct (1) a systematic review of HAI prevention studies and (2) in-depth quantitative analyses using administrative claims, in-depth clinical data, and organizational surveys of VAD centers. For aim 2, we will apply a mixed methods patient tracer assessment framework to conduct semistructured interviews, field observations, and document analysis informed by findings from aim 1 at 5 high-performing (ie, low HAIs) and 5 low-performing (ie, high HAI) centers, which will be examined using a mixed methods case series analysis. For aim 3, we will build upon the findings from the previous aims to develop and field test an HAI preventive toolkit, acquire stakeholder input at an annual cardiac surgical conference, disseminate the final version to VAD centers nationwide, and conduct follow-up surveys to assess the toolkit’s adoption.

**Results:**

The project was funded by the Agency for Healthcare Research and Quality in 2018 and enrollment for the overall project is ongoing. Data analysis is currently under way and the first results are expected to be submitted for publication in 2019.

**Conclusions:**

This mixed methods study seeks to quantitatively assess the determinants of HAIs across clinical centers and qualitatively identify the context-specific facilitators and barriers for attaining low HAI rates. The mixed data findings will be used to develop and disseminate a stakeholder-acceptable toolkit of evidence-based HAI prevention recommendations that will accommodate the specific contexts and needs of VAD centers.

**International Registered Report Identifier (IRRID):**

PRR1-10.2196/14701

## Introduction

### Use of Durable Ventricular Assist Device to Treat Advanced Heart Failure

Heart failure affects nearly 5.7 million Americans and is a contributing cause of 1 in 9 deaths [1]. It is estimated that the prevalence of heart failure will increase by 46% from 2012 to 2030 [2]. The condition is the second costliest in terms of Medicare expenditures (approximately US $30.7 billion annually) [1]. Durable ventricular assist device (VAD) therapy is reserved for patients with advanced heart failure who have a poor estimated 1-year survival [3,4]. Technological advances using newer magnetically levitated centrifugal continuous-flow VADs have improved patient survival and decreased adverse event rates compared with older continuous-flow axial technology [5,6]. Currently, the estimated VAD survival is approximately 50% at 4 years, accompanied by significant improvements in functional status and quality of life [7,8].

### Risk of Device-Related Health Care–Associated Infection

Patients with VADs are at a heightened risk for device-related and nondevice-related health care–associated infection (HAI) despite a highly protocolized perioperative and postoperative course. The nature of durable VAD therapy requires an uninterrupted external power source connected to the patient through a driveline (ie, a percutaneous lead to provide power and control to the implantable pump), which serves as a potential source for the development of HAIs given its connectivity between the patient and the external environment [9]. In addition, VAD therapy is frequently associated with other infections that are nondevice-related, including pneumonia and surgical site or bloodstream infections [10,11]. VAD patients are at a unique risk for HAIs given (1) the burden of multiple preoperative comorbid conditions; (2) the invasive nature of VAD implantation; (3) hemodynamic instability that often occurs at the time of device implantation; (4) a common feature of all devices, a percutaneous lead; (5) extended intensive care unit stays; and (6) concurrent need for invasive monitoring.

The majority of HAIs occur within 90 days after a VAD implantation, with a decreased but ongoing risk beyond the 90-day period [12-16]. More than 3000 patients undergo VAD implantation in the United States annually, with nearly 6 out of every 10 patients developing a HAI following the procedure [16-22]. Development of an HAI is associated with a 6-fold risk of 1-year mortality and incurs additional treatment expenditures (US $264,000-US $869,000 per patient) [23,24]. Notably, infectious complications secondary to VAD implantation are the second leading cause of death for this population (16% of all deaths) [25].

### Variation in Health Care–Associated Infection and Preventive Strategies

Large variation exists in both the rate of HAIs and, more notably, the adoption of preventive strategies (eg, checklists, effective teamwork, and unit and center leadership) across clinical centers [26,27]. A 2017 study noted significant variation in the choice and duration of antimicrobial prophylaxis across 20 VAD centers (ie, one that implants a VAD or treats a patient within 90 days of implantation of a VAD) [26]. Although researchers have reported the benefit of preventive strategies, adoption by the clinical community varies [28-33]. Researchers have noted improved outcomes among cardiac surgery patients being cared at health systems with stronger provider teamwork (as captured in the configuration of social networks among providers), suggesting that a high level of provider teamwork may promote the prevention of HAIs [33,34]. Moreover, a 2018 study reported reductions in HAIs with the adoption of evidence-based practices within the setting of coronary artery bypass grafting procedures [35]. However, further investigation is required to understand the optimal HAI prevention strategies that have been adopted and how high-performing centers (ie, those with lower HAI rates) enhance the implementation of these strategies relative to low-performing centers.

### Conceptual Framework Guiding the Study

Figure 1 shows the conceptual framework illustrating the determinants of HAIs and informing the areas of investigation in this study. We hypothesized that patient and caregiver, process, provider, and device-related risk factors as well as a center’s local strategies, context, and resources are associated with the development of HAIs. Moreover, we hypothesized that, after accounting for perioperative risk factors, a center’s local strategies, context, and resources are associated with HAIs. Centers with lower HAI rates may leverage resources (eg, infection prevention staff) to reduce barriers to and increase facilitators of infection prevention strategies (eg, antimicrobial prophylaxis regimen) to prevent HAIs. Furthermore, we envision that a modular, action-oriented HAI toolkit, taking into account a center’s local strategies, context, and resources, could guide clinical teams (via evidence-based recommendations and educational tools) in preventing HAIs.

**Figure 1 figure1:**
[figure not shown]
Conceptual model for health care–associated infection development and impact. VAD: ventricular assist device.

### Rationale for the Study

Few studies have focused on understanding both the optimal strategies for HAI prevention after VAD implantation as well as the approaches for enhancing the local adoption of these practices. Relying on administrative claims or clinical data is insufficient for identifying novel HAI practices, let alone understanding the characteristics of center- and unit-level strategies and contexts contributing to HAIs. To address this research gap, this mixed methods study seeks to identify recommendations for preventing the most clinically significant HAIs after VAD implantation. First, we plan to characterize key determinants of HAIs using quantitative approaches. Subsequently, we plan to identify context-specific promoters and barriers to preventing HAIs across low- and high-performing centers using qualitative approaches. More importantly, a multidisciplinary study team will use both findings to develop an action-oriented modular toolkit that provides evidenced HAI prevention recommendations, which accommodates the specific needs of individual centers. This project will contribute to research knowledge and interventions aimed at preventing HAIs by encouraging field-wide adoption of evidence-based practices.

## Methods

### Overall Study Design

As shown in Figure 2, we will use an explanatory sequential mixed methods design to address 3 aims: (1) identify determinants of center-level variability in HAI rates; (2) develop comprehensive understanding of barriers and facilitators for achieving low center-level HAI rates; and (3) develop, iteratively enhance, and disseminate a best practices toolkit for preventing HAIs that accommodates various center contexts. In aim 1, we will (1) conduct a systematic review of existing HAI prevention studies to compile a list of current prevention strategies and (2) conduct in-depth analyses using a unique merged dataset of all Food and Drug Administration (FDA)–approved VADs implanted in Medicare beneficiaries as well as an organizational survey administered to VAD centers. Our systematic literature review and analysis of provider social networks (including physician and nonphysician providers) will inform areas of investigation and identify the sample of high-performing and low-performing centers for aim 2. In aim 2, we will develop a comprehensive understanding of local facility and context-sensitive approaches contributing to variability in HAI rates through site visits at a sample of centers to reveal routine and novel HAI determinants and identify feasible solutions for ensuring local adherence to HAI prevention practices. In aim 3, we will (1) field test a prototype toolkit, (2) present an iteratively enhanced version to key VAD clinical stakeholders (eg, surgeons, clinical coordinators, nurses, and cardiologists) attending an annual conference in the field of cardiac surgery to optimize the toolkit’s usability and acceptability before national dissemination, and (3) conduct a follow-up survey to assess the adoption of the proposed toolkit. The human subjects’ applications for secondary use of the Interagency Registry for Mechanically Assisted Circulatory Support (INTERMACS) and Medicare data (HUM00155687) and for administration of center surveys (HUM00157335) have been approved by the institutional review board of the University of Michigan.

**Figure 2 figure2:**
[figure not shown]
Overall study design. HAI: health care–associated infection; INTERMACS: Interagency Registry for Mechanically Assisted Circulatory Support.

### Aim 1: Identify Determinants of Center-Level Variability in Health Care–Associated Infection Rates

To address this aim, we will first conduct a systematic review of interventional HAI prevention studies. Second, we will supplement the clinical dataset with (1) data from an electronically distributed survey of VAD centers to identify HAI prevention strategies not already tracked through INTERMACS and (2) center-specific measures of provider social network configurations using a merged INTERMACS-Medicare dataset [7,36]. Third, we will calculate center-specific 90-day HAI rates. Fourth, we will model variability in and identify determinants of centers’ HAI rates using this enhanced clinical dataset. We hypothesize that (after accounting for perioperative risk factors through INTERMACS) process, provider, device, and center- and unit-specific risk factors will be significant determinants of HAI rates. Findings will inform the sampling plan and focus on aim 2 activities.

#### Datasets Used for Aim 1

##### Center for Medicare and Medicaid Services Files

Given that Medicare is the largest US health care payer, Center for Medicare and Medicaid Services (CMS) is the sole national data source of exhaustive claims for noninstitutional and institutional providers. The CMS files contain data about (1) beneficiary (eg, age, diagnoses, and type of benefits); (2) institutional admissions; (3) provider services; (4) outpatient, hospice, home health agency, and skilled nursing facility services; and (5) prescription drugs (eg, heart failure medications). Each file contains data about the date and location of services and payments. We will characterize the social networks of providers (eg, nurse practitioners, physician assistants, and physicians) as a measure of provider teamwork. Following precedent from prior research on physician social networks, we will restrict these networks to specific provider specialties (eg, anesthesiology and surgery) that are most likely to be directly involved with the care of VAD patients [33,34,37-41]. Determination of relevant providers will be made through consultation with clinicians and through descriptive assessments of claims data.

##### American Hospital Association Survey

Data from this annual survey, to be merged with CMS files, contain center-specific structure and organizational measures (eg, size, urban or rural location, teaching status, affiliation with networks, training programs, ownership, staffing levels, and types of surgical services provided).

##### Interagency Registry for Mechanically Assisted Circulatory Support

INTERMACS is a multicenter, Joint Commission–recognized, nationally audited database of FDA-approved VADs. INTERMACS contains extensive data regarding (1) preimplant details (eg, age and comorbid diseases); (2) operative details (eg, device type and operative duration); (3) patient status until death, cardiac transplantation, or device removal; (4) adverse events (eg, device malfunctions); and (5) functional status, neurocognition, and health-related quality of life. INTERMACS monitors device-related (driveline, exit cannula, pump pocket, and pump interior) and nondevice-related (positive blood cultures, central line associated sepsis, pulmonary, urinary tract, mediastinum, peripheral wound, gastrointestinal) HAIs.

##### Center Survey

The survey, informed by a systematic review of the literature and prior work, will identify potential HAI determinants that are not available through existing data sources [42,43]. Independent of our network analysis, the survey will be designed to address determinants spanning the patient’s full clinical trajectory (preoperative, implantation, postoperative, rehabilitation, and discharge). Surveys will be sent to the center’s designated VAD coordinator, implanting surgeons, and heart failure cardiologists involved in the center’s VAD program. The use of Web-based survey software (ie, Qualtrics) will allow for the creation, distribution, storage, and analysis of survey instruments, with advanced features (eg, randomization of question ordering).

Preliminary survey drafts will be developed based on a conceptual framework and by our investigative team of clinical and research experts, with input from survey and decision science experts. We will test the draft survey instrument with key stakeholders at selected centers with low and high HAI rates to ensure readability, face validity, and completeness of response options. Interviews will be conducted by Web-based teleconference in real time as the draft survey is completed to solicit qualitative feedback on survey content. The survey will be revised based on this feedback.

We will use evidence-based strategies to maximize survey response rate and minimize nonresponse bias, especially as a function of a center’s HAI rate. For example, the email invitation will be personalized, and the survey length will be limited. In addition, nonrespondents (VAD coordinator, surgeon, and cardiologist) will be contacted by the study team as necessary. Our team will provide respondents with a small gift card after completing the survey.

#### Sample Size

We project analyzing data among 9339 VAD patients receiving durable VAD from 2008 to 2017. We will administer surveys to potential respondents (VAD coordinator, surgeon, and cardiologist) from an estimated 153 VAD centers.

#### Analytic Approach

First, we will conduct a systematic review of the published literature to identify established HAI preventive practices [44,45]. Second, we will use survey responses to identify provider and institutional practices that contribute to center variability in HAI rates. Third, we will use our linked Medicare-INTERMACS datasets to identify preoperative, intraoperative, and postoperative factors that contribute to center variability in HAI rates.

##### Primary Endpoint

Our primary endpoint is any HAI 90 days after device implant. We will account for HAI competing risks (eg, death and device removal) and other censoring (follow-up less than 90 days) using time-to-event analysis. Furthermore, we will use 2 approaches for modeling HAI risk. First, we will use the Cox proportional hazards model. We will adjust for surgery year and season and investigate interactions by key biological variables (eg, patient age, sex, and race). We will account for patient demographics (eg, age and sex), disease characteristics (eg, pulmonary disease), and surgical history (eg, prior cardiac surgery) and study the effect of intraoperative care (eg, cardiopulmonary bypass duration) and postoperative care (eg, duration of intubation). We will use the Lasso variable selection method to assess variables for model inclusion [46]. We will handle the multilevel structure (eg, patients are nested within centers) using the robust sandwich variance–based inference or frailty model approach. On the basis of the final fitted model, effects of risk factors will be quantified by hazards ratios and tested by score tests. Second, we will use random survival forest, an extension of the random forest method to right-censored time-to-event data, to model the effects of risk factors nonparametrically [47-49]. The final model will be an ensemble average of fitted trees from bootstrap samples.

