##### Teamwork and Communication as Quality Measurement

Provider social networks represent a measure of teamwork and communication that are associated with the quality of care [34]. In prior validation work, shared patients between providers, identified using unique provider identifiers found in claims data, have been found to correspond closely to surveyed provider network patterns [33,51]. We will characterize mapped VAD networks using a measure known as assortativity, which can capture the degree to which providers from different specialties and clinical disciplines are interconnected and, thus, better equipped for collaboration and teamwork [52]. We will incorporate this measure as a covariate in our statistical models [34]. Recent network research has drawn attention to several challenges in characterizing assortativity in social networks. First, global (ie, network level) measures of assortativity may mask considerable local (ie, node level) variation in cross-group (eg, specialty) interaction [53]. Second, common network data practices (eg, unipartite projection of a bipartite network) may lead to bias in values of standard assortativity measures [54]. To overcome these challenges, we plan to use state-of-the-art techniques for evaluating assortativity in social networks, including multiscale measures of assortativity (which allow for measuring assortativity at the node level) and comparison of assortativity on our observed networks with null (ie, random network) models.

Claims data do not map perfectly to true care patterns; therefore, our network measures may include false negatives and false positives. To assess for these biases, we will run several sensitivity analyses, motivated by prior work on missing data and thresholding techniques in the study of social networks [55-57]. Using Monte Carlo simulations, we will randomly drop increasingly larger fractions of providers and relationships in our observed networks, recompute our network measures, and then rerun our statistical models to assess bias attributed to false negatives. In additional simulations, we will also gradually add larger fractions of random providers and relationships to our observed networks to assess sensitivity to false positives.

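### Hazard ratios for center factors are read from a final model that may also hold the strategies and care they work through, and no model for their total association is specified

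*Protocol article*

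**What the plan says.** The Primary Endpoint section adjusts a Cox model for patient demographics, disease characteristics and surgical history. In the same model it will "study the effect of intraoperative care (eg, cardiopulmonary bypass duration) and postoperative care (eg, duration of intubation". On selection it says: "We will use the Lasso variable selection method to assess variables for model inclusion". On inference it says: "On the basis of the final fitted model, effects of risk factors will be quantified by hazards ratios and tested by score tests". No order of entry and no adjustment set per determinant is stated.

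Center-level factors reach the modeling through two other places. For the network measure of teamwork, the section Teamwork and Communication as Quality Measurement says: "We will incorporate this measure as a covariate in our statistical models". For survey and network data together, the Aim 1 overview says: "we will model variability in and identify determinants of centers’ HAI rates using this enhanced clinical dataset".

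The causal picture is in Conceptual Framework Guiding the Study: "Centers with lower HAI rates may leverage resources (eg, infection prevention staff) to reduce barriers to and increase facilitators of infection prevention strategies". The strategy named there as an example is the antimicrobial prophylaxis regimen. The same section hypothesizes that "after accounting for perioperative risk factors, a center’s local strategies, context, and resources are associated with HAIs". The Aim 1 overview states its hypothesis in similar terms: "after accounting for perioperative risk factors through INTERMACS) process, provider, device, and center- and unit-specific risk factors will be significant determinants".

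**The concern.** By the protocol's own account, resources lie upstream of prevention strategies, and strategies lie upstream of infection. If both enter one model, the coefficient for resources is only what remains once the measured strategies are held fixed. The same applies to teamwork or staffing wherever these change the care delivered and that care is also in the model. A hazard ratio near 1 could then mean that the factor has no association with HAI, or that its association runs through something else in the model. The planned output cannot tell these apart. Hazard ratios for resources and for intubation duration would also sit in one table of determinants while answering different questions.

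This arises even if every care variable is recorded before any infection, so it is separate from reverse causation. It matters because Aim 1 findings steer the focus of Aim 2 and the content of the toolkit. Resources and teamwork are the levers the study set out to examine, and they are the factors most exposed.

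**Working it through.** The article states no power, effect size or mediated share, so there is no planned figure to reproduce. The check has two parts.

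**1. What the sections fix when read together**

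- Primary Endpoint fixes where effects are read (the final Cox model) and names intraoperative and postoperative care among the factors studied in it.
- The teamwork section and the Aim 1 overview bring network and survey measures into the modeling.
- The Conceptual Framework places strategies downstream of resources. The overlap of upstream and downstream candidates therefore exists without assuming any route through bypass or intubation time.
- Exploratory Analyses fits models with and without a group of factors, but compares expected with observed numbers and states no order of entry. As described, it gives no hazard ratio or test for a center factor adjusted only for preimplant factors. The random survival forest has no separate adjustment set either.

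**2. How much attenuation is possible (illustration)**

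Inputs from the article: 9339 patients and an estimated 153 centers, so 9339/153 = 61.0 patients per center. Nearly 6 in 10 patients develop an HAI, which is not stated as a 90-day figure; if it were, 0.6 × 9339 ≈ 5603 patients.

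Assumptions:

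- X is a standardized center factor and P a standardized patient risk score.
- M is a measured downstream variable with unit variance: M = a·X + 0.3·P + noise.
- Log hazard = b·M + d·X + 0.3·P + center effect (SD 0.3), with b = 0.4.
- The baseline hazard is 0.0085 per day, with censoring at 90 days. At average covariates this gives 1 − exp(−0.0085 × 90) = 53% with an HAI; about 55% was seen in the simulation.
- There were 20 data sets per row, each with two Cox fits: X and P, then X, P and M.

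Approximate expectation: the total log HR is d + a·b and the log HR given M is d, so the share removed is a·b/(d + a·b). The simulated share is 1 − ln(HR with M)/ln(HR without M).

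| a | d | Expected share | HR without M | HR with M | Simulated share |
|---|---|---|---|---|---|
| −0.50 | 0 | 0.20/0.20 = 100% | 0.830 | 0.998 | 99% |
| −0.50 | −0.1 | 0.20/0.30 = 67% | 0.760 | 0.911 | 66% |
| −0.25 | −0.1 | 0.10/0.20 = 50% | 0.829 | 0.905 | 47% |
| −0.25 | −0.2 | 0.10/0.30 = 33% | 0.759 | 0.825 | 30% |
| −0.10 | −0.2 | 0.04/0.24 = 17% | 0.804 | 0.826 | 13% |
| 0 | −0.2 | 0% | 0.834 | 0.828 | −4% |

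For row 2, for example: 1 − ln(0.911)/ln(0.760) = 1 − 0.093/0.274 = 66%. The small negative value in the last row is consistent with a Cox hazard ratio moving slightly away from 1 when a prognostic variable is added, and with simulation error. Lasso selection and competing events were not simulated.

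**The case against.** **The conditional association is the authors' own question.** Both hypotheses are stated after adjustment for perioperative risk factors. This stands in part, and it is a reason to keep the planned model. The term is not defined, however. The Aim 1 overview adjusts through INTERMACS, which holds operative details, yet lists process and device factors as determinants rather than adjusters. The Strengths section presents the network analysis as capturing differences that traditional patient risk factors miss, which points toward adjustment for patient factors only.

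**The protocol does not say that center factors act through bypass or intubation time.** This is correct. A reader might infer that the planned model removes the very pathway the protocol describes by holding those two variables fixed. The text does not support that: its stated route runs from resources through prevention strategies. A route through bypass or intubation time is plausible but inferred.

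**Not every determinant is tied to one fit.** A reader might infer that all determinants come from a single model. The article speaks of statistical models in the plural, lists survey and linked-data steps separately, and adds a random survival forest and the with-and-without comparison. Lasso may also drop either variable. This stands as a limit on the claim, but none of these analyses is described as giving a total association.

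**Order of entry belongs in the analysis plan.** Normally so. Here the article itself states the model from which effects are read.

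**Bypass and intubation time may carry case severity.** This also stands. The introduction lists hemodynamic instability at implantation and extended intensive care stays among the reasons for high risk. An estimate adjusted only for preimplant factors can therefore absorb residual case mix.

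**The consequence is limited.** Aim 2 centers are chosen first on HAI rates, site visits examine resources and strategies directly, and no rule drops a factor whose hazard ratio is not significant. That is why this is an improvement rather than a failure of the design.

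**Conclusion.** The point holds as a gap in what the planned hazard ratios can show. Upstream center factors, the strategies they are said to act through, and delivered care are candidates for one Lasso-selected Cox model. Effects are read from that model, and no model for the total association of a center factor is specified.

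The size is unknown. On assumed path strengths, about 0% to 99% of the log hazard ratio is removed, and the 99% case assumes complete mediation. Only the part running through variables that are both measured and retained is lost, so it would be wrong to conclude that center effects are removed altogether. Nor do the documents support replacing the conditional model or rewriting the hypotheses, since a conditional association is partly intended and care variables may reflect severity. Reporting both associations is a low-cost improvement.

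**What to change.** Keep the planned model and prespecify a staged sequence beside it:

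1. Preimplant patient and disease factors, surgery year and season, plus center structure, resources and teamwork. Estimate and test these center factors here.
2. Add center strategies.
3. Add device, intraoperative care and postoperative care.

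Report both hazard ratios for each center factor, labelled as the total association and as the association remaining after measured care. State that no center factor will be classed as not a determinant on the fully adjusted model alone. In the Conceptual Framework and the Aim 1 overview, say which variables perioperative risk factors covers.

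The cost is some wording and a few more fits on data the study already plans to use. The drawbacks are more than one model to present and possible residual case mix in the first-stage estimate, which is why both are shown.
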